### Intervention

All subjects entering the study will be centrally randomised at the baseline visit into one of three study arms, in a 1:1:1 ratio:

*Arm 1* will receive at the baseline visit ADA 80 mg SC loading dose followed a week later by 40 mg every-other-week starting at week 1. They will also receive MTX oral at the baseline visit, with initial dose of 15 mg/week, increasing up to 25 mg/week.

*Arm 2*: MTX with the same schedule as in arm 1.

*Arm 3*: ADA with the same schedule as in arm 1.

In addition to the study drugs, topical adjunctive eye medication will be allowed according to standard practice (intraocular pressure-lowering medication, cycloplegic agents, artificial tears, topical non-steroidal anti-inflammatory drugs…). The use of any biologic therapies with a potential therapeutic impact in NIUs, live vaccines, any other ISD besides the study drugs, intraocular GCs implants or intraocular surgery will be prohibited for the duration of the trial.

To ensure a balance of patients across treatment groups and uveitis anatomic locations, patients will be stratified according to the main site of ocular inflammation (intermediate, OR posterior/panuveitis). Randomisation will not be stratified by site due to the small-expected number of subjects per site.

Block randomisation will ensure that an equal number of patients are randomised to each study arm.

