Visual Functioning Questionnaire-25	(X)‡	(X)‡					X									X	X		
Hospital Anxiety and Depression Scale	(X)‡	(X)‡					X									X	X		
Haematology/chemistry	X	(X)§	X	X	X	X	X		X		X		X		X	X	(X)		
Monitor adverse events		(X)	X	X	X	X	X	X	X	X	X	X	X	X	X	X	X	X	X
Monitor concomitant medication	X	X	X	X	X	X	X	X	X	X	X	X	X	X	X	X	X	X	X
Review of patient diary			X	X	X	X	X	X	X	X	X	X	X	X	X	X	(X)		
Perform drug accountability			X	X	X	X	X	X	X	X	X	X	X	X	X	X	(X)		
Assessment of direct and indirect costs			X	X	X	X	X	X	X	X	X	X	X	X	X	X	(X)		
Dispense study drugs		X	X	X	X	X	X	X	X	X	X	X	X	X	X		(X)		
Proteomic blood sample	(X)¶	(X)¶					X									X	X		
Pharmacogenetic blood sample	(X)¶	(X)¶																	
Adalimumab levels and antiadalimumab antibodies	(X)¶	(X)¶					X**			X**						X**	X**		

*Chest X-ray will be performed at the 52 weeks/early termination visit in case the patient had a positive TB test at baseline.

†Cerebral MRI will be performed only in those subjects with intermediate uveitis or signs of intermediate uveitis.

‡Values from the baseline visit or from a screening visit up to 14 days before the baseline visit will be used as the values from the baseline visit.

§Total blood count, renal and liver function test from up to 4 weeks before the baseline visit will the required before entering the study.

¶Blood sample will be drawn after signature of the informed consent, as soon as possible, ideally before start of oral GCs.

**Blood samples for the antiadalimumab antibodies will be drawn the week before visits 16, 28, 52. Early termination and relapse visits, up to 24 hours before the patient is scheduled to receive the ADA dosage, and always before the medication is taken.

††Only in women in childbearing

FET, final (w52)/early termination visit; ISD, Immunosuppressive Drug; NYHA, New York Heart Association; PPD, Purified protein derivative; TNF, Tumor Necrosis Factor; Unsch, unscheduled visit; w, week.

After the trial, all patients will return to standard care and will be able to continue with their assigned study medication.

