#### Planned methods of statistical analysis for efficacy-related objectives

The primary analysis will be a Mantel–Haenszel test (MHT), stratified by NIU location, comparing the combination therapy arm and the single ISDs arms (both arms combined), and performed in the ITT set. Achievement of the Good Clinical response will be considered the binary response variable: those subjects achieving a Good Clinical versus those not achieving the outcome (regardless the cause). The exposure variables will be the treatment arm: those subjects receiving combination therapy versus those receiving either monotherapy. Uveitis location will be the strata: intermediate uveitis versus posterior OR panuveitis. If the results of the primary analysis are significant, then pairwise comparisons using MHT stratified by NIU location will be carried out. P values of the pairwise comparisons will be adjusted using the Bonferroni method. No interim efficacy-related analysis will be carried out.

Secondary efficacy-related analyses are designed to test the hypothesis that treatment assignment affects a given outcome, after controlling for selected covariates. Details can be found at table 4.

**Table 4 T4:** Planned methods of statistical analysis for efficacy-related secondary outcomes

Outcome variable	Statistical analysis
Complete abrogation of the ocular inflammatory signs, which is achieved within the first 16 weeks of the study, no treatment failure due to safety or intolerability; compliance with the initial (up to week 16) oral GCs tapering protocol and completion of all study visits from baseline to 16 weeks	MHT, stratified by NIU location. If p-value<0.05, pairwise comparisons using MHT stratified by NIU location will be carried out with Bonferroni adjustment of the pairwise p-values
EQ5D	GEE models nested by patient^70 71^ and adjusted by study visit (continuous) and treatment arm (discrete) will be carried out, using a Gaussian family and Identity as link function. Different covariable structures will be tested (independent and exchangeable) and compared using the Bayesian Information Criteria. Time x study arm interactions will assess different effects of time in the evolution of the outcome by arm. P-value<0.05 will be considered as a significant interaction
Visual Functioning Questionnaire-25 Hospital Anxiety and Depression Scale	Changes between Baseline and w16, and the FET visit will be compared between treatment groups using ANOVA

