Active chorioretinal lesions; active retinal vascular lesions; macular oedema; ACC; vitreous haze and loss of CVA secondary to inflammation at baseline, week 16, week 52 and relapse visit	MHT, stratified by NIU location. If p-value<0.05, pairwise comparisons using MHT stratified by NIU location will be carried out with Bonferroni adjustment of the pairwise p-values
The time to inflammatory relapse between groups, defined as the time from visit 16 weeks until end of the study, loss of follow-up or appearance of at least one ocular inflammatory manifestation, in those individuals achieving a Good Clinical Response by visit 16 week	Time to relapse between arms will be analysed using log-rank test at a two-sided significance level of 5%. Dropouts due to reasons other than inability to maintain a Good Clinical Response will be considered as censored observations at the time of dropping out. Only subjects able to achieve a Good Clinical Response by visit week 16 will be analysed. We will consider both the time until the onset of the first inflammatory manifestation, each inflammatory manifestation, the first inflammatory manifestation that does not resolve in the following 4 weeks and each inflammatory manifestation that does not resolve in the following 4 weeks.
Best-corrected visual acuity during follow-up	GEE models
Assessment of anti-ADA antibodies (AAA) at weeks 15, 27, 51 and relapse	MHT, stratified by NIU location. If p-value<0.05, pairwise comparisons using MHT stratified by NIU location will be carried out with Bonferroni adjustment of the pairwise p-values
Direct and indirect cost, and incremental cost effectiveness ratios	Cost utility and cost-effectiveness analysis from the perspectives of the National Health System and the Society will be performed. EQ5D scores will derive utility values representing health related quality of life. QALYs will be calculated by the area under the curve assuming a linear evolution of EQ5D values between visits. The average number of QALYs per patient will be calculated for each study arms. Effectiveness will be defined using our primary efficacy outcome. An average cost per patient will be calculated for each study arm, including direct (drug cost, outpatient and inpatient care and other medical cost) and indirect cost (home care, productivity loss): Incremental cost-effectiveness ratios will be calculated, using the MTX monotherapy arm as comparison

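### The cost-utility plan describes arm-average QALYs and names no adjustment for baseline EQ-5D, so part of a chance baseline difference enters the incremental QALY and precision is lost

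*Protocol article*

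**What the plan says.** The last row of Table 4 (protocol article, section on planned methods for efficacy-related objectives) sets out the health-economic analysis in steps. Utilities come from EQ-5D. Then "QALYs will be calculated by the area under the curve assuming a linear evolution of EQ5D values between visits". Then "The average number of QALYs per patient will be calculated for each study arms". An average cost per patient is found for each arm, and "Incremental cost-effectiveness ratios will be calculated, using the MTX monotherapy arm as comparison". For the cost-effectiveness part, "Effectiveness will be defined using our primary efficacy outcome". The row names no regression model, covariate or baseline term.

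The sentence that introduces Table 4 says that secondary analyses test the effect of treatment "after controlling for selected covariates. Details can be found at table 4". The separate EQ-5D row describes GEE models "adjusted by study visit (continuous) and treatment arm (discrete) will be carried out"; baseline EQ-5D is not listed there either.

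Baseline EQ-5D is collected. Table 3 schedules it at screening or baseline, at week 4 and every four weeks after that, and its footnote explains which record counts as baseline: "Values from the baseline visit or from a screening visit up to 14 days before the baseline visit will be used". Under Intervention, "patients will be stratified according to the main site of ocular inflammation (intermediate, OR posterior/panuveitis"). No other stratification factor is named.

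**The concern.** A QALY built as an area under the curve starts from the baseline utility, and later utilities in the same patient tend to follow it. Randomisation is stratified only by uveitis location, so arms of 64 balance on baseline EQ-5D only by chance. If the arm averages are simply subtracted, part of whatever imbalance occurs appears as a QALY gain or loss. The predictable between-patient variation also stays in the error term.

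The incremental QALY is the denominator of the cost-utility ratio. A small denominator makes that ratio sensitive to shifts of this kind. Cost-utility, from health-system and societal perspectives, is a stated secondary objective in Table 1.

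**Working it through.** **The plan's own figures.** The article gives no QALY, EQ-5D standard deviation or ICER figure to reproduce. The one figure needed is the arm size. Sample size determination states 54 per arm and 15% losses: 54 / 0.85 = 63.5, rounded up to 64, as stated. (The 54 fits combination versus both monotherapy arms pooled, 66% versus 43%, two-sided 0.05, 80% power: 54.4 before rounding.) Nothing below changes the sample size.

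**Assumptions, none given in the documents.** Utility SD 0.15 to 0.30, the same at every visit; within-patient correlation rho of 0.3 to 0.7, the same between any two visits; complete EQ-5D at weeks 0, 4, ..., 52. Each ratio is formed against methotrexate, so each compares two arms of 64.

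**Step 1: weight of baseline in the QALY.** With linear interpolation, week 0 has weight w0 = 2/52 = 0.038, each visit from week 4 to week 48 has 4/52 = 0.077, and week 52 has 2/52. The sum of squared weights is S = 0.074.

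**Step 2: how much of a baseline difference carries over.** The slope of QALY on baseline is b = w0 + (1 − w0) × rho. The direct weight is small; most of the carry-over comes through the correlation.

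**Step 3: variance removed by adjustment.** Relative to the utility variance, the QALY variance is V = S + (1 − S) × rho. The share explained by baseline is b² / V.

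| rho | b | V | share of variance removed | reduction in SE |
|---|---|---|---|---|
| 0.3 | 0.33 | 0.35 | 30% | 17% |
| 0.5 | 0.52 | 0.54 | 50% | 29% |
| 0.7 | 0.71 | 0.72 | 70% | 45% |

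**Step 4: size on the QALY scale.** The SE of the baseline difference is SD × √(2/64): 0.027 at SD 0.15, 0.035 at 0.20 and 0.053 at 0.30. The shift from a one-SE imbalance is b × SE, from 0.009 (SD 0.15, rho 0.3) to 0.038 (SD 0.30, rho 0.7). For a 1.96-SE imbalance the range is 0.017 to 0.074.

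**Step 5: a central example.** At SD 0.20 and rho 0.5, the shift is 0.52 × 0.035 = 0.018. The SE of the QALY difference is 0.0354 × √0.537 = 0.026 unadjusted, and 0.026 × √(1 − 0.50) = 0.018 adjusted.

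**Step 6: effect on the ratio.** Assume a true gain of 0.05 QALY (not in the documents) and hold incremental cost fixed. A shift of +0.018 multiplies the ratio by 0.05 / 0.068 = 0.74. A shift of −0.018 multiplies it by 0.05 / 0.032 = 1.56.

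**The case against.** The strongest reply is that the row never says its averages are crude. A regression-adjusted mean is also an average per arm, and the lead-in to Table 4 points towards covariate control. The article condenses a full protocol and refers to a separate analysis plan; neither is shown, and either could specify the adjustment. A reader might infer that the plan commits to a crude comparison, and the text does not support going that far. What it does support is narrower: the article names Table 4 as the place where covariates are detailed, other rows there state their stratification or adjustment, and this row goes through the calculation from utilities to ratio with none. Unadjusted averages are the plain reading, though not a printed word.

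Three other stronger readings fail.

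- A reader might infer that an imbalance passes in full into the result. Only a fraction does, and the baseline value's direct weight is 3.8%.
- A reader might infer that every planned ratio is affected. The cost-effectiveness ratio uses Good Clinical Response and does not depend on EQ-5D. The trial title and the key secondary outcomes in Table 5 likewise name cost-effectiveness, not cost-utility.
- A reader might infer that the unadjusted analysis is invalid. Under randomisation it is unbiased on average, and its standard error already allows for chance imbalance. The cost is lost precision, and bias only conditional on the imbalance observed.

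It is also fair that the sizes rest on assumed inputs, and that the ratio would stay imprecise after adjustment: in the central example, an SE of 0.018 against an assumed gain of 0.05.

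**Conclusion.** The point holds in limited form. As written, the cost-utility analysis uses arm-average QALYs with no named adjustment for baseline utility or uveitis location, and the row does not supply the covariates that the introduction to Table 4 promises.

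If the averages are used as they stand, about 0.33 to 0.71 of a chance baseline EQ-5D difference enters the incremental QALY, and about 30% to 70% of the variance of that difference could have been removed. These ranges rest on an assumed common within-patient correlation of 0.3 to 0.7. The absolute sizes also need an assumed utility SD, and the effect on the ratio needs an assumed gain. The primary analysis, the sample size and the Good Clinical Response ratio are untouched. It is a worthwhile improvement to a secondary analysis, not a flaw in the trial's main conclusion.

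**What to change.** In the health-economic row of Table 4, and in the analysis plan, state that incremental QALYs are estimated by regressing each subject's QALY on treatment arm, baseline EQ-5D utility and uveitis location (the randomisation stratum), and that the adjusted differences from methotrexate form the denominators of the cost-utility ratios. Arm averages can still be reported descriptively. If the unseen plan already says this, one clause in Table 4 is enough.

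The cost is wording only. Baseline EQ-5D is already scheduled in Table 3, and no visit, measurement or additional subject is needed.

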### Objectives and outcome variables

The trial main hypothesis is that the use of combination therapy with MTX and ADA will be more effective in inducing and maintaining ocular inflammatory inactivity than either drug given in monotherapy.

The *primary efficacy objective* is to establish which treatment strategy results in a higher proportion of subjects achieving a complete and maintained resolution of the ocular inflammation, on an intent to treat basis. The *primary efficacy outcome* will be the proportion of patients achieving a *Good Clinical Response* between the combination therapy arm and the single ISD arms. This outcome is defined as a complete resolution of the ocular inflammatory signs (including active chorioretinal lesions, active retinal vascular inflammation, uveitis macular oedema, presence of anterior chamber cells and presence of vitreous haze), achieved within the first 16 weeks of the study and maintained during follow-up until the end of the study (week 52); furthermore, there must not be a treatment failure due to safety or intolerability; the subject must adhere to the initial (up to week 16) oral GCs tapering protocol; all study visits from baseline to 16 weeks must be completed and at the final visit (week 52), the subject must be treated with up to 7.5 mg/day of oral prednisone (or equivalent) and up to two times a day of prednisolone acetate 1% (or equivalent). The *secondary efficacy objectives* and outcomes variables can be found at table 1.

**Table 1 T1:** Efficacy-related secondary objectives and outcome variables

Objective	Outcome variable
To compare the fraction of subjects who achieve a complete inflammatory ocular inactivity by week 16	Complete abrogation of the ocular inflammatory signs, which is achieved within the first 16 weeks of the study, no treatment failure due to safety or intolerability; compliance with the initial (up to week 16) oral GCs tapering protocol, and completion of all study visits from baseline to 16 weeks
To compare several Patient-Reported Outcomes Measures (health-related and vision-related quality of life, anxiety and depression) between treatment strategies	EuroQuol 5D-5L Visual Functioning Questionnaire-25 Hospital Anxiety and Depression Scale

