To compare the presence of the clinical components of the Good Clinical Response variable between treatment strategies during follow-up	Active chorioretinal lesions; active retinal vascular inflammation; macular oedema; ACC; vitreous haze and loss of CVA secondary to inflammation at baseline, week 16, week 52 and relapse visit
To compare the time to relapse after week 16 between treatment strategies	The time to inflammatory relapse between groups, defined as the time from visit 16 weeks until end of the study, loss of follow-up or appearance of at least one ocular inflammatory manifestation, in those individuals achieving a Good Clinical Response by visit 16 week
To compare the evolution of visual acuity during follow-up	Best-corrected visual acuity (BCVA) during follow-up
To compare the development of anti-adalimumab antibodies during the follow-up, between those subjects treated with monotherapy and combination therapy	Assessment of anti-ADA antibodies (AAA) at week 15, 27, 51 and relapse
To assess the cost-utility and cost-effectiveness from both a Health System and a Societal perspective of the combination therapy and the ADA monotherapy compared with MTX given alone	Direct and indirect cost, and incremental cost effectiveness ratios. Drug costs will be calculated individually for each patient taking as reference the price published in 2022 by the Health Ministry for the Spanish Health System. Outpatient and inpatient care, other medical cost, home care and productivity loss will be estimated based on the data from eSalud database^68^ and from the Minimum Basic Data Set of the Spanish Health Ministry.^69^

ADA, adalimumab; GC, glucocorticoid; MTX, methotrexate.

Security-related objective will establish which treatment strategy has better tolerability. Safety outcomes will be collected in the form of AEs, physical examination and laboratory tests throughout the treatment period and up to 70 days after the last dose in this study. Gender of the subjects will be taken into account.^53^

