#### Sample size determination

*ADA arm*: after 1 year (50 weeks) of treatment, 20.3% of NIU patients achieved an outcome similar to our *primary efficacy outcome*.^28^

*MTX arm*: after 6 months of treatment, 65% of NIU patients achieve also similar outcome;^64^ we estimate that of those patients, 18%^65^ and 16%^66^ will be unable to maintain our outcome due to AEs and inefficacy, respectively; therefore, at 1 year, 43% will achieve our *primary efficacy outcome*. This figure will be assumed as the percentage of subjects treated with monotherapy achieving the primary efficacy outcome.

*MTX+ADA arm*: we will assume that combination therapy will increase the percentage of subjects achieving our *primary efficacy outcome* by 23% compared with the monotherapy arms.

To detect statistically significant differences between groups with a power of 80% and a significance level of 0.05, it will be necessary to recruit 54 patients per study arm (162 in total). Since the follow-up period is 52 weeks, losses of 15% will be assumed, increasing the sample size to 64 patients per study arm (192 patients in total). In order to test the difference between the treatments, superiority or relevant clinical improvement has been considered from a delta of 5% of the effect.

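### Cost-effectiveness ratios are planned only against methotrexate, so no combination-versus-adalimumab ratio is stated and the combination can look better value than it is

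*Protocol article*

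**What the plan says.** Table 1 (Objectives and outcome variables) states the economic objective as the cost-utility and cost-effectiveness "of the combination therapy and the ADA monotherapy compared with MTX given alone". Table 4 (Planned methods of statistical analysis for efficacy-related objectives) carries this into the analysis, where the ICERs are to be obtained "using the MTX monotherapy arm as comparison".

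The same row of Table 4 plans the ingredients for every arm: "An average cost per patient will be calculated for each study arm", and "The average number of QALYs per patient will be calculated for each study arms". For the cost-effectiveness ratio, as distinct from the cost-utility ratio, "Effectiveness will be defined using our primary efficacy outcome", that is, Good Clinical Response.

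The Abstract and the Study overview present the trial as a comparison of the efficacy, safety and cost-effectiveness of MTX, ADA and the two together. Table 5 lists cost-effectiveness as a key secondary outcome. No willingness-to-pay threshold, acceptance rule or method for ICER uncertainty is stated.

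**The concern.** The three arms are mutually exclusive strategies. The usual full incremental analysis compares each with the next less costly strategy that is not dominated. Here both ADA and the combination are compared with MTX. The combination's ratio is therefore an average over the whole step from MTX, and it does not change with the ADA result.

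ADA is the combination's nearest alternative by drug content: under Intervention, the combination arm receives ADA on the ADA arm's schedule, plus MTX. If ADA alone delivers most of the benefit, the MTX-referenced ratio credits that benefit to the combination. It can then look acceptable when the step from ADA to the combination is poor value, and someone choosing among three options could be pointed to the wrong one.

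**Working it through.** The protocol gives no cost, QALY or ICER to reproduce. All costs, QALYs and thresholds below are assumptions, in arbitrary currency units. Only the response rates come from Sample size determination:

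- MTX: "therefore, at 1 year, 43% will achieve our" primary outcome, which reproduces as 65% × (1 − 0.18 − 0.16) = 42.9%. The same figure is assumed for both monotherapy arms.
- ADA: 20.3% is cited from an earlier trial.
- Combination: 23% above monotherapy, read as percentage points, so 43% + 23 = 66%.

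**When the two references disagree.** Let ADA cost A more than MTX, and the combination m more than ADA. Let E be mean effect, with positive gains for the combination over both drugs. The combination-versus-ADA ICER, m/(E_comb − E_ADA), exceeds the combination-versus-MTX ICER, (A + m)/(E_comb − E_MTX), exactly when

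(E_comb − E_ADA)/(E_comb − E_MTX) < m/(A + m).

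With A = 6,000 and a 23-point gain over MTX:

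| m | m/(A + m) | gain over ADA must be below |
|---|---|---|
| 500 | 500/6,500 = 7.7% | 1.8 points |
| 1,000 | 1,000/7,000 = 14.3% | 3.3 points |
| 2,000 | 2,000/8,000 = 25% | 5.8 points |

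**Cost per responder.** Assume costs of 3,000 (MTX), 9,000 (ADA) and 9,500 (combination), with 43% response on MTX and 66% on the combination. Combination versus MTX is 6,500/0.23 = 28,261, whatever ADA does. Combination versus ADA is:

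| ADA response | combination versus ADA |
|---|---|
| 20.3% | 500/0.457 = 1,094 |
| 43% | 500/0.23 = 2,174 |
| 55% | 500/0.11 = 4,545 |
| 64% | 500/0.02 = 25,000 |
| 65% | 500/0.01 = 50,000 |
| 68% | combination dominated |

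In the first two rows ADA costs more than MTX and does no better, so it is dominated and MTX is the correct reference.

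**Cost per QALY.** Take the same costs, QALYs of 0.60 (MTX) and 0.85 (combination), and a threshold of 30,000. Combination versus MTX is 6,500/0.25 = 26,000 throughout. Net monetary benefit is 30,000 × QALY − cost: MTX 15,000, combination 16,000.

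| ADA QALY | combination versus ADA | ADA net benefit | best arm |
|---|---|---|---|
| 0.70 | 500/0.15 = 3,333 | 12,000 | combination |
| 0.84 | 500/0.01 = 50,000 | 16,200 | ADA |
| 0.85 | extra cost, no gain | 16,500 | ADA |
| 0.86 | dominated | 16,800 | ADA |

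The MTX-referenced ratio is below the threshold in all four rows, but the combination is the best choice only in the first.

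**A second set of assumed inputs.** Take MTX 0.70 QALY at 1,000, ADA 0.80 at 2,500 and combination 0.81 at 3,000. Against MTX, ADA is 1,500/0.10 = 15,000 and the combination 2,000/0.11 = 18,182. Combination versus ADA is 500/0.01 = 50,000. At a threshold of 25,000 the net benefits are 16,500, 17,500 and 17,250, so ADA is best although the combination's ratio against MTX passes.

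**The case against.** Four points on the other side have force.

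- **The plan is consistent with itself.** Tables 1 and 4 name the same reference. The main hypothesis, that the combination "will be more effective in inducing and maintaining ocular inflammatory inactivity than either drug given in monotherapy", concerns efficacy. A reader might infer that the economic section contradicts it, but the documents do not support that. The issue is the choice of comparator.
- **The combination is costed, and ADA is examined.** A reader might infer that the combination is never costed against ADA, or that ADA is never tested for dominance. Neither follows. Mean costs and QALYs are planned for every arm, and ADA versus MTX shows directly whether MTX dominates ADA. When cost and effect both rise from MTX to ADA to the combination, ADA is extendedly dominated exactly when its MTX-referenced ICER exceeds the combination's. The missing ratio follows by subtracting the two planned contrasts.
- **No decision rule is stated.** A reader might infer that the planned analysis would accept the combination. The protocol sets no threshold, so a wrong conclusion would come from how the ratio is read.
- **Small gains over ADA would show elsewhere.** Arm-level response would reveal them, as would the pairwise efficacy tests. However, those tests follow only if the primary comparison against the pooled monotherapies is significant, and they do not address cost.

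These points limit the concern without removing it. The reference arm is fixed in two places, so it is more than detail left to an unseen plan, and an analysis that follows the wording need not report the ratio that separates the combination from ADA.

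**Conclusion.** The concern holds in a limited form. The protocol plans ICERs for ADA and the combination only against MTX and states no combination-versus-ADA ICER or sequential comparison, although it sets out to compare the cost-effectiveness of all three strategies. The MTX-referenced ratio can make the combination look acceptable when the step from ADA is poor value.

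This is a possibility that depends on the results. It needs ADA to remain on the efficiency frontier and the combination's gain over ADA to be small relative to its added cost. The 1.8 to 5.8 points rest on the assumed cost differences and on a 23-point gain over MTX. At the protocol's own response rates the problem does not arise on the responder scale, provided that ADA costs more than MTX. The protocol gives no planning values for QALYs, so that reassurance does not extend to the cost-utility ratio. The primary analysis is unaffected.

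**What to change.** Amend the economic rows of Tables 1 and 4 so that the three arms are ordered by mean cost, dominated and extendedly dominated arms are removed, and each remaining ICER is reported against the next less costly non-dominated arm. That gives combination versus ADA wherever ADA remains. Net monetary benefit for all three arms over stated thresholds would be an equivalent presentation. Keep the MTX-referenced ratios as supplementary results. Bootstrap and acceptability-curve details can be left to the analysis plan.

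The cost is a change of wording and a little extra health-economic analysis. Costs and EQ-5D are already collected in every arm, so no further patients, visits or data are needed.
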